#### Sample size

Sample size was calculated for the primary outcome measure of PPC with a type I error rate of .05 and a type II error rate of 0.20 (80% power). Estimates of the incidence of PPCs vary throughout the literature dependent upon criteria used for diagnosis but best estimates suggest a PPC rate (after thoracotomy and amenable to physiotherapy interventions) of between 10–25% occurs in this population with routine physiotherapy care [4,14], Assuming a PPC rate of 20% in the Control Group and 5% in the Treatment Group (thus a 15% difference in PPCs), 84 subjects in each group are required. Allowing for an estimated loss to follow up rate of 9% (based on similar studies) a sample size of 184 subjects (92 per group) is necessary to demonstrate sufficient power for the primary outcome. Because there are no randomised trials that include a control group on which to accurately base this sample size calculation, an interim analysis will be undertaken when total n = 80.

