### Outcome measurement

Outcome measures, instruments used and timeframes for measurement are summarised in Table 2.

**Table 2 T2:** Summary of outcome measurements

**Primary Outcomes**	**Measurement instrument**	**Time point**
PPC	8 point item score (see Table 3)	Postop daily to discharge

**Secondary Outcomes**	**Measurement instrument**	**Time point**

LOS	Retrospective from patient information database	At discharge
SPADI	13 items scored on 11 point Likert scale	Preop, at discharge, 1 month postop, 3 months postop
ROM of shoulder flexion, elevation through abduction and external rotation (subgroup)	Plurimeter – V inclinometer	Preop, at discharge, 1 month postop, 3 months postop
MMS of shoulder abduction, flexion and internal rotation (subgroup)	Hand held dynamometer (Lafayette Instruments)	Preop, 1 month postop, 3 months postop
HRQoL	Short Form 36 v2 (NZ)	Preoperative, 1 month postop, 3 months postop
Pain	Body charts and verbal rating scale (end descriptors 0 = no pain and 10 = worst pain possible)	Preop, at discharge, 1 month postop, 3 months postop

Key : HRQoL – Health related quality of life, LOS – length of postoperative hospital stay, MMS – muscle strength, NZ – New Zealand, Postop – postoperative, PPC – postoperative pulmonary complication, Preop – preoperative, ROM – range of movement, SPADI – shoulder pain and disability index.

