#### 5. Isometric muscle strength

In a subgroup of patients living within a 60 km radius of Auckland Hospital, muscle strength will be measured preoperatively, one month and three months postoperatively by a blinded assessor using a handheld manual muscle tester (Lafayette instruments) which has been shown to have moderate to high interrater and intrarater reliability [30]. Measurements will be made of those of muscle groups that have been divided during surgery and thus may affect muscle strength. The measures are:

a. Shoulder flexion

b. Shoulder abduction

c. Shoulder internal rotation

d. Shoulder extension

All measures are taken in the same position as described for ROM testing with the position of the dynamometer established in the same way using the easily identifiable surface markings of 1 cm above the elbow crease (for flexion), 1 cm above the lateral epicondyle (for abduction), 1 cm above the olecranon (for extension) or the skin crease (usually middle) between the radial styloid process and the head of the ulna (for internal rotation). The starting position is with the arm at the side with one gripped fist width between the distal end of the humerus and chest wall, the elbow flexed to 90° and the forearm in the mid prone position. This position was chosen due to the potential for subjects to be unable to commence muscle strength measures in 90° or 45° glenohumeral abduction as recommended by some authors [31,32]. Resistance is applied against the direction of shoulder movement for three to five seconds. The "make" (rather than "break") technique is used requiring the examiner to resist a maximal voluntary contraction by the subject which is essentially an isometric contraction and has been shown to have high interrater and intrarater reliability even in inexperienced examiners [33].

Standardised instructions and verbal encouragement is given and, after one practice contraction, each movement is measured three times with one minute between measures. Subjects report maximum pain during each movement on a 0 – 10 verbal rating scale. In keeping with other authors the maximum intensity of pain for each movement will be recorded [33-35].

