### Data analysis

Analyses will be conducted using an intention to treat principle for all randomised subjects. Demographic data will be analysed using descriptive statistics, Chi squared and Independent t tests or parametric equivalents.

A Chi squared test will be used to determine if there is any significant difference in the incidence of PPC between groups. LOS will be tested for normality of data. If normally distributed an Independent t test will be used to calculate the differences in mean LOS between groups and in differences in LOS in those subjects who do and do not develop PPCs. Data will be presented as mean differences with 95% confidence intervals. If data are not normally distributed a non parametric Mann Whitney U test will be used. The absolute risk reduction and number needed to treat will also be calculated for the primary outcome of PPC. Further between group comparisons for repeated measures of interval data (such as shoulder ROM, shoulder muscle strength, ADL and HRQoL) will be made using repeat measures ANOVA. Significant results will be analysed using post hoc tests such as the Scheffe F test. The alpha level for all statistical analyses will be set at 0.05.

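### Repeated-measures ANOVA for shoulder, strength and quality-of-life outcomes leaves the preoperative value unadjusted and needs complete series, which conflicts with the intention-to-treat promise

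*Protocol article*

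**What the plan says.** The Data analysis section of the protocol article covers "repeated measures of interval data (such as shoulder ROM, shoulder muscle strength, ADL and HRQoL") and says that the between-group comparisons "will be made using repeat measures ANOVA". It continues: "Significant results will be analysed using post hoc tests such as the Scheffe F test". It does not say whether the preoperative value is a covariate or a level, whether group or group-by-time is the treatment test, or how incomplete series are handled. The same section opens with "Analyses will be conducted using an intention to treat principle for all randomised subjects" and closes with "The alpha level for all statistical analyses will be set at 0.05".

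Table 2 (Outcome measurement) gives the occasions for SPADI, shoulder movement and pain as "Preop, at discharge, 1 month postop, 3 months postop". For strength, the section on isometric muscle strength says "muscle strength will be measured preoperatively, one month and three months postoperatively". Table 2 gives the same three occasions for quality of life, whereas the Abstract adds discharge. Allocation takes place on the first postoperative day (Recruitment and randomisation).

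The Sample size section says: "Allowing for an estimated loss to follow up rate of 9% (based on similar studies").

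**The concern.** The preoperative measurement precedes allocation, so it cannot carry a treatment effect. If it is one of the repeated levels, the group main effect averages it in with the visits that can carry one. The group-by-time F test avoids that averaging. However, it asks whether the profiles differ in any way at all, and it returns a p-value rather than a difference at one or three months. By contrast, the article promises mean differences with confidence intervals for length of stay, and an absolute risk reduction for pulmonary complications.

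Classical repeated-measures ANOVA also excludes any subject with a gap in the series. That does not fit a promise to analyse everyone randomised when loss is expected. If patients who recover poorly are the ones who miss visits, the result may be biased as well as less precise.

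At stake are H2 (shoulder movement, strength and function) and the quality-of-life aim.

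**Working it through.** **Inputs from the article.** 84 per group needed, 92 per group recruited (184 in total), 9% loss, alpha 0.05. SPADI, shoulder movement and pain have four occasions. Strength, and quality of life under Table 2, have three. I take ADL to mean SPADI.

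**Assumptions (the article gives none of these).** Outcome SD of 1; equal correlation r = 0.3, 0.5 or 0.7 between any two occasions; a true effect of 0.4 SD at every follow-up in the base case; two-sided tests.

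**The plan's own figure.** 84 × 1.09 = 91.6, so 92 per group and 184 in total, as stated. The article gives no power figure for the repeated outcomes.

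**Dilution of the group main effect.** With T occasions, one of them before randomisation, a constant difference d appears as d(T−1)/T.
- T = 4: 0.4 × 3/4 = 0.30 SD.
- T = 3: 0.4 × 2/3 = 0.27 SD.

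**Power, n = 84 per arm, noncentral F.** Formulas, with numbers for T = 4 and r = 0.5:
- Group main effect: v = (1+(T−1)r)/T = 0.625; λ = n × 0.30²/(2v) = 84 × 0.09/1.25 = 6.05 on 1 and 166 df; power 69%.
- Group-by-time: λ = (n/2) × Σ(effect − mean effect)²/(1−r) = 42 × 0.12/0.5 = 10.08 on 3 and 498 df; power 76%.
- Baseline-adjusted mean of k = 3 follow-ups: v = (1+(k−1)r)/k − r² = 0.667 − 0.25 = 0.417; λ = 84 × 0.4²/(2 × 0.417) = 16.13 on 1 and 165 df; power 98%.
- Baseline-adjusted 3-month contrast: v = 1 − r² = 0.75; λ = 84 × 0.4²/1.5 = 8.96 on 1 and 165 df; power 85%.

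Power in % at r = 0.3 / 0.5 / 0.7:

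| Scenario (SD at successive follow-ups) | Group main effect | Group-by-time | Adjusted follow-up mean | Adjusted 3-month contrast |
|---|---|---|---|---|
| 4 occasions, constant 0.4 | 80 / 69 / 59 | 60 / 76 / 94 | 97 / 98 / >99 | 77 / 85 / 95 |
| 3 occasions, constant 0.4 | 65 / 56 / 48 | 61 / 76 / 94 | 93 / 95 / 99 | 77 / 85 / 95 |
| 4 occasions, growing 0.1, 0.3, 0.5 | 56 / 45 / 38 | 70 / 85 / 98 | 83 / 85 / 93 | 92 / 96 / 99 |
| 4 occasions, waning 0.4, 0.3, 0.2 | 56 / 45 / 38 | 46 / 61 / 85 | 83 / 85 / 93 | 27 / 32 / 44 |

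The 84 per arm applies to SPADI and quality of life only. Shoulder movement and strength are measured in the subgroup living within 60 km, whose size is not given. As an illustration, with 40 per arm, 4 occasions, a constant 0.4 SD effect and r = 0.5, the first three columns become 39, 42 and 78%.

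**Complete series.**
- 9% as one overall loss rate, as the article gives it: 184 × 0.91 = 167.
- 9% missing independently at each of three follow-ups (assumption): 184 × 0.91³ = 139, or 75%.
- The same with two follow-ups: 184 × 0.91² = 152.

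**Scheffe threshold,** √(k × F(0.95; k, df)): about 3.76 for all contrasts among 8 group-by-time cells (k = 7), 3.34 for 6 cells (k = 5) and 2.8 if confined to the 3-df interaction. A single planned contrast needs about 1.96.

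**The case against.** The strongest reply is that the article is condensed, and that model terms and missing-data rules normally belong in an analysis plan that is not shown. This stands in part. A reader might infer that the article states that the preoperative value is a level and that incomplete subjects are dropped, but it states neither. The first is the natural reading of a list of occasions with no covariate. The second is a property of the classical method. The method itself is named, however, so an analysis plan would have to replace it and not merely fill in detail.

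Several stronger readings are tempting and are not supported:
- *Every test is diluted.* Only the group main effect is. H2 concerns recovery, for which group-by-time is the natural ANOVA term, and there the preoperative level serves as the reference.
- *Baseline adjustment always gains power.* With a growing effect, group-by-time equals the adjusted follow-up mean at r = 0.5 (85% each) and beats it at r = 0.7 (98% against 93%).
- *Only 75% of subjects would be kept.* That applies a single overall 9% to each of three follow-ups, one of them at hospital discharge.
- *The Scheffe hurdle is 3.76.* Scheffe is offered as an example, and 3.76 is the largest of three plausible thresholds.
- *Three months should be the main contrast.* It does well if the effect grows and badly if it wanes (27/32/44%), so this is a choice for the investigators.

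A mixed model does not settle everything either. It omits subjects with no follow-up value at all, and it is valid only if data are missing at random.

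**Conclusion.** The point holds as a worthwhile improvement to the secondary analyses. The named method leaves the role of the preoperative value and the treatment term open. Used in its classical form, it cannot analyse everyone randomised once the expected 9% loss occurs.

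For a constant effect, the main-effect reading understates the difference by a quarter (4 occasions) or a third (3 occasions). Under the base assumptions with 4 occasions, its power is at least 17 percentage points below that of the adjusted follow-up mean (80 against 97% at r = 0.3), and the gap widens as r rises. The group-by-time reading falls short by 37, 22 and about 5 points at r = 0.3, 0.5 and 0.7, and that shortfall can reverse if the effect grows and the correlation is high. All power figures rest on the assumed effect sizes and correlations; for shoulder movement and strength they would be lower, because that subgroup is smaller.

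The chi-squared test for pulmonary complications, its sample size and the length-of-stay comparison are unaffected.

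**What to change.** Replace repeated-measures ANOVA and the Scheffe follow-up with a linear mixed model on the post-randomisation visits. Enter the preoperative value as a covariate, include group-by-visit terms and an unstructured covariance, and include every randomised subject with at least one follow-up value. State that validity rests on missing at random.

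Report the adjusted group difference with a 95% confidence interval at each visit and averaged over follow-up. Prespecify which of these is the main contrast for H2. The average is the steadier choice across the effect shapes examined; a single visit is reasonable if the investigators have a clinical reason for it.

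Reconcile the Abstract and Table 2 on whether quality of life is measured at discharge, because that sets the number of visits in its model.

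The cost is analysis wording and slightly more analysis work. No new data are needed.

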## Discussion

This study uses a single blind randomised controlled design to investigate the efficacy of physiotherapy interventions in the prevention of complications following pulmonary resection via open thoracotomy. The benefits of physiotherapy for these patients have not been established despite being widely recommended as an integral part of standardised postoperative care. To our knowledge this will be the first randomised controlled trial using a Control Group with no physiotherapy to study the efficacy of physiotherapy interventions in preventing pulmonary and shoulder complications in this population.

The role of prophylactic physiotherapy, particularly the value of deep breathing exercises, following other types of major surgery has been recently challenged as a result of evidence from RCTs [36,37]. Prior to the current study being initiated, we determined, using a postal survey, that the majority of physiotherapists continue to prophylactically treat patients after open thoracotomy [19]. Most commonly deep breathing and airway clearance manoeuvres, early ambulation and shoulder exercises were used for patients following thoracic surgery [19]. Whether this level of intervention is necessary in this patient group is currently unknown. Given the findings of the survey which determined commonality in practices across physiotherapy providers, we have chosen to use standardised minimum physiotherapy interventions (see example in Figure 2) rather than utilising a pragmatic design where therapists would be free to choose their own interventions. This will enable both reproducibility and consistency. Delivery of the programme is by the attending ward physiotherapist whose identity will vary according to workload allocations thus increasing the external validity of the study. Deviations from the standardised protocol will be recorded.

For all subjects, the self reported measures of shoulder function will provide clinically relevant measures of shoulder recovery following surgery. Studies have shown ROM impairment and functional status to be significantly associated [38,39] and therefore any subject not achieving recovery of shoulder function scores within 20 per cent of preoperative status will be offered outpatient follow up physiotherapy as necessary. As subjects undergoing pulmonary resection in our surgical unit are drawn from a wide geographical area, follow up measures of shoulder ROM and MMS are not feasible for all patients. Thus we determined that patients living within 60 kilometres of the unit who were able to attend outpatient appointments will form a subgroup who will undergo ROM and muscle strength testing as additional measures.

It is anticipated that data collection will be completed by late 2008 and that this study will contribute to the increasing evidence base into the effects of physiotherapy interventions following major surgery.
